#### Footwear assessment

Minor trauma that results in tissue damage or a break in the cutaneous barrier of the skin is most commonly due to ill-fitting or inappropriate footwear, which is frequently implicated in the development of foot ulcers due to rubbing and repetitive trauma [41, 55]. Reiber et al. [55] found that a minor traumatic event was one of the main component causes for the development of foot ulcers, which was present in 77 % of the foot ulcer pathways. In addition, pressure from footwear caused the minor traumatic event in 55 % of the participants [55]. Assessment of footwear fit, general features, type and condition is based on the recommendations of the validated footwear assessment tool described by Barton et al. [65]. Footwear will be deemed inappropriate if any of the following are present:Poor shoe fit (i.e. length, width and depth);Inappropriate shoe style (i.e. for foot type, activity, foot problems etc.) or;Poor shoe condition [65].

#### Dermatological assessment

Skin and nail pathologies have been found to be predictive of foot ulceration in people with diabetes in prospective studies [27, 55]. The grading of xerosis severity will be evaluated using the Xerosis Severity Scale, which has been used in several randomised trials [66–68]. Skin pathology will be recorded if any of the following are present:Hyperkeratosis [16, 69];Heloma dura [16, 69];Uraemic pruritus [70, 71];Xerosis (graded in accordance with the Xerosis Severity Scale) [67];Calciphylaxis [18, 72];Other.

Nail pathology will be recorded if any of the following are present:Half-and-half nail [70, 71];Absent lunula [70, 71];Onychomycosis [27, 69];Onychocryptosis [69];Onychauxis [69];Other.

#### Foot health care behaviours and podiatry attendance

Foot health care behaviours will be considered ‘poor’ if the participant answers “no” to three or more of the following questions:Do you inspect your feet daily?Do you avoid walking barefoot?Are you able to reach your feet?Do you treat your own nails and skin lesions? (e.g. calluses or corns)Have you ever seen a podiatrist before?

Regular podiatry attendance will be determined with the following question:How many times have you seen a podiatrist in the last 12 months?

### Follow-up appointment

The follow-up appointment will occur 12 months after the baseline appointment. Satellite participants will be followed-up face-to-face in the dialysis units, whereas home-therapy participants will be contacted via telephone. Prior to the follow-up appointment, participant medical records will be screened for any recent deaths or discharges. This is to ensure that the families of participants who died during the study are not contacted.

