### Participant recruitment, screening and eligibility criteria

Participants will be recruited from *satellite* dialysis units (i.e. centres where patients attend for dialysis treatment) and *home-therapy* dialysis units (i.e. dialysis treatment is performed at home) throughout Eastern Health, Austin Health and Monash Health in Melbourne, Victoria, Australia. Recruitment and collection of baseline data is anticipated to occur between January 2014 and December 2014.

Prospective participants will be identified by liaising with the renal dialysis nurses in the satellite and home-therapy dialysis units, according to the study eligibility criteria. Those attending the satellite dialysis units will be screened face-to-face, whereas respondents to the mail-out (i.e. home-therapy participants) will be screened for eligibility via telephone.

Patients attending for dialysis in the satellite units will be approached by the chief investigator ([name]) during their dialysis treatment. If interested, they will be offered verbal and written information about the project and will have the opportunity to join the study at the time of meeting the researcher, or will be offered a follow-up telephone call. Alternatively, prospective participants may contact the research team at their own convenience if they are interested in participating.

Patients in the home-therapy dialysis program will be mailed a covering letter and an information package, along with an invitation to contact the research team by telephone or email if they are interested in participating. Patient lists from the home-therapy dialysis unit will be screened prior to mailing to confirm that addresses are current and to exclude any recent deaths or discharges.

To be included in the study, participants will be eligible if they:(i)have ESRD and are clinically stable on dialysis (haemodialysis or peritoneal dialysis);(ii)are at least 18 years of age and;(iii)are cognitively aware (i.e. they can provide informed consent).

Participants will be excluded if they:(i)have insufficient English skills to provide informed consent or follow instructions during the project and;(ii)are unwilling to give informed consent to participate.

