• Chronic glomerulonephritis	Inflammatory arthritis (documented diagnosis in medical history of a type of inflammatory arthritis e.g. gout, rheumatoid arthritis, psoriatic arthropathy)	
• Polycystic kidney disease		
• Reflux nephropathy		
• Renovascular disease		
• Vasculitis		
• Unknown	Other (any other documented medical conditions)	
• Other		
Dialysis treatment		
• Haemodialysis		
• Continuous ambulatory peritoneal dialysis		
• Automated peritoneal dialysis		
Duration of dialysis (months)		

An average of the three latest blood test results (i.e. C-reactive protein, serum albumin, total calcium, serum phosphate, parathyroid hormone, glycated haemoglobin and haemoglobin) will be obtained at baseline

Previous studies have demonstrated that health-related quality of life is negatively impacted by the presence of a diabetic foot ulcer [28, 29]. Generic health status will be assessed with the short-form 36 version 2.0 health survey (SF-36v2®). The SF-36v2® has been extensively validated (construct, concurrent, content, criterion and predictive validity) and provides a reliable measure of physical and mental health in a range of populations [30–33]. The SF-36v2® is a 36 question survey that covers eight health domains that are summarised under two components, (i) a physical component summary including: physical functioning, role-physical, bodily pain and general health, and (ii) a mental component summary including: vitality, social functioning, role-emotional and mental health [34].

A non-invasive foot assessment will screen for the suspected risk factors for foot ulceration. Neurological (Table 2), arterial (Table 3), biomechanical (Table 4), footwear (Table 5) and dermatological (Table 6) assessments will be conducted. Data will also be collected on previous history of lower extremity complications (Table 7) and foot health care behaviours, including podiatry attendance (Table 8).

**Table 2 Tab2:** Baseline data: neurological assessment

Neurological assessments	Equipment	Procedure	Diagnosis/study definition
Known peripheral neuropathy	N/A	Medical record review.	History of peripheral neuropathy documented in medical records.

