### Primary outcome

The primary outcome in this prospective observational cohort study will be:new foot ulcer(s) (including new and reoccurring ulcers).

A foot ulcer will be defined as a ‘full thickness skin break that is distal to the ankle joint, and may extend into or through the dermis and involve deeper structures such as bones, tendons, joint capsules and ligaments’ [27, 73]. Current foot ulcers (i.e. ulcers present at baseline appointment) that healed and re-ulcerated during the follow-up period will also be recorded as new foot ulcers. At the 12-month follow-up appointment, participants will self-report whether they developed a new foot ulcer since their baseline appointment. This information will be verified by reviewing participants’ medical records. All new foot ulcers documented at the follow-up appointment will be differentiated into ‘new’ and ‘reoccurring’ ulcers. All medical histories of participants will be reviewed to determine whether any new foot ulcers occurred during the 12-month follow-up period.

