### Secondary outcomes

Secondary outcome data will also be collected at the 12 month follow-up appointment including:number of new foot ulcers;time to onset of new foot ulcer(s);new lower extremity amputation(s) (including level of amputation and reason for amputation);episodes of infection of the foot or lower extremity (including type of infection);episodes of osteomyelitis;foot-related hospitalisations (including reason for admission, length of stay and foot-related treatments/procedures received during hospital admission);revascularisation procedure(s) of the lower extremity (including type of procedure);new podiatry interventions (e.g. nail reduction, prescription of foot orthoses);kidney transplantation and;mortality (including primary and secondary causes of death).

All secondary outcomes will be self-reported by participants and then verified by reviewing medical records. All medical histories of participants will be reviewed to determine whether any of the secondary outcomes occurred during the 12-month follow-up period. The time to onset of new foot ulcer(s) will be defined as the ‘number of days between the baseline appointment and the development of a new foot ulcer’. Medical records will be referred to for the first documented encounter of the new foot ulcer and this date will be recorded. A lower extremity amputation will be defined as a ‘complete loss of any part of the lower extremity [74], including any digit, partial foot amputation or higher’. Lower extremity amputations resulting from accidental trauma unrelated to ESRD or the presence of a tumour will not be recorded. Lower extremity amputations will be classified as major or minor. A major amputation will be documented if there is loss of limb above the ankle, or minor amputation if below the ankle [74, 75]. Mortality data will also be collected at the follow-up appointment. Date of death (including primary and secondary causes of death) will also be recorded from reviewing patient medical histories. For those participants that die during the study period, hospital medical records will be reviewed to assess for the primary and secondary outcomes up until the date of death.

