Continuous variables	Categorical variables
Participant characteristics	Participant characteristics
• **Age**	• **Male sex**
• **Body mass index**	• **Current smoker**
Health-related quality of life (SF-36v2®)	• **Living alone**
• Physical Component Score	Comorbidities
• Mental Component Score	• **Diabetes mellitus**
Comorbidities	• **Retinopathy**
• **Duration of diabetes**	• **Peripheral neuropathy**
Dialysis-related variables	• **Peripheral arterial disease**
• **Duration of dialysis**	• **Arterial calcification**
Laboratory blood tests	• **Hypertension**
• C-reactive protein	• **Dyslipidaemia**
• Serum albumin	• **Ischaemic heart disease**
• Total calcium	• **Congestive cardiac failure**
• Serum phosphate	• **Cerebrovascular disease**
• Parathyroid hormone	• Osteoarthritis
• Glycated haemoglobin (HbA1c)	• Inflammatory arthritis
• Haemoglobin	Lower extremity complications
Other	• **Previous foot ulceration**
• Peak plantar pressures	• **Current foot ulcer present at baseline**
	• **Previous lower extremity amputation**
	Other
	• Reduced range of motion of the 1^st^ metatarsophalangeal joint
	• **Foot deformity**
	• **Inappropriate/ill-fitting footwear**
	• Skin pathology
	• Nail pathology
	• Poor foot health care behaviours
	• Regular podiatry attendance

Potential confounding variables that will be considered in the regression models are boldface

Intra-examiner reliability of the assessor ([name]) will be evaluated using ICCs for continuous data and the weighted kappa (κ) statistic for ordinal data. To assess the strength of linear correlation between the two measurements (i.e. to detect random and systematic errors) [25], ICCs and corresponding 95 % CIs of the type (3, 1) will be calculated for single measures and type (3, *k*) for average measures. ICC values >0.75 indicate good reliability, ICCs ranging from 0.50 to 0.75 imply moderate reliability and ICCs <0.50 suggest poor reliability [25]. The 95 % Limits of Agreement will also be calculated to examine the level of agreement between the two measurements [25, 79]. Absolute agreement in addition to linear weighted kappa will be calculated for ordinal data to determine the proportion of the total amount of agreement between the two measurements that is not explained by chance [80, 81]. Weighted kappa values >0.8 represent excellent agreement, >0.6 substantial levels of agreement, 0.4 to 0.6 moderate agreement and <0.4 poor to fair agreement [25].

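### Table 9 omits dialysis setting, modality and health service from the candidate confounders, although recruitment route and follow-up contact differ by setting

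*Protocol article*

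**What the plan says.** Participants come from satellite and home-therapy units "throughout Eastern Health, Austin Health and Monash Health in Melbourne, Victoria, Australia", that is, three health services. Under participant recruitment, satellite patients are approached in person during dialysis and screened face-to-face. Home-therapy patients receive a mailed package, must contact the team themselves, and are screened by telephone.

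The split continues at 12 months: "Satellite participants will be followed-up face-to-face in the dialysis units, whereas home-therapy participants will be contacted via telephone" (Follow-up appointment).

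The Primary outcome section sets one procedure for everyone. First, "participants will self-report whether they developed a new foot ulcer since their baseline appointment". Then "This information will be verified by reviewing participants’ medical records". In addition, "All medical histories of participants will be reviewed to determine whether any new foot ulcers occurred during the 12-month follow-up period". For the onset date, Secondary outcomes states: "Medical records will be referred to for the first documented encounter of the new foot ulcer and this date will be recorded".

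Table 1 records dialysis treatment as haemodialysis, "Continuous ambulatory peritoneal dialysis" or automated peritoneal dialysis. Table 9 lists the risk factors and marks in bold the potential confounders for the regression models. Under its heading "Dialysis-related variables" the only entry is duration of dialysis. Setting, modality and health service appear nowhere in the table, in bold or otherwise. Stratum-specific analyses are named for diabetes and sex only.

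**The concern.** Setting determines how a participant enters the cohort and how that participant is contacted at the end. It may also affect how soon and how often staff see and document a foot problem, since satellite patients attend a centre for dialysis and home patients do not. The Cox models use both event status and event date, and the date comes from documentation. If documentation is more complete or earlier in one setting, a risk factor that is commoner there would pick up part of that difference. A true difference in ulcer risk between settings, modalities or services would act in the same way.

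The plan's own safeguard cannot reveal this. A confounder is kept if it changes an estimate by 10% or more, or is significant at 5%, but only listed variables are tested. The article presents multi-centre recruitment and control of confounding as improvements on earlier studies, so the omission bears on a claimed strength.

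**Working it through.** The point turns on no figure stated in the plan, so there is none to reproduce. The check compares the two settings, then asks how large a carry-over could be.

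**1. The two settings side by side**

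| Step | Satellite | Home therapy |
|---|---|---|
| Invitation | in person, during dialysis | mailed; patient must respond |
| Screening | face-to-face | telephone |
| 12-month contact | face-to-face | telephone |
| Ulcer source | self-report, verified in records; all records reviewed | same |
| Foot examination at follow-up | none specified | none specified |
| Onset date | first documented encounter | same |

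Selection and contact differ. The ascertainment procedure does not. What can still differ is how complete and how prompt the underlying records are.

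**2. What is available and what is listed**

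- Modality: collected (Table 1), not in Table 9.
- Setting: known from recruitment, not in Table 9.
- Health service: known from recruitment, not in Table 9.
- Duration of dialysis: in Table 9, in bold.

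Modality is not a full substitute for setting, because the haemodialysis category in Table 1 is not divided by place of treatment.

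**3. Possible size of the ascertainment effect**

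The documents give no detection rates and no home-therapy share, so every input here is an assumption. Let s_sat and s_home be the probabilities that a true ulcer is recorded. Let h1 and h0 be the home-therapy shares among those with and without some risk factor. Assume no true effect of setting and no false positives.

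- Observed home:satellite ratio when the true ratio is 1 = s_home / s_sat. With s_sat = 0.95 and s_home = 0.90, 0.80, 0.70, 0.60, this is 0.95, 0.84, 0.74, 0.63.
- Bias factor on the other risk factor's risk ratio = [(1 − h1)·s_sat + h1·s_home] / [(1 − h0)·s_sat + h0·s_home].

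For h1 = 0.10, h0 = 0.30 and s_home = 0.60: (0.90 × 0.95 + 0.10 × 0.60) / (0.70 × 0.95 + 0.30 × 0.60) = 0.915 / 0.845 = 1.083.

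| s_home | 20% vs 20% | 15% vs 25% | 10% vs 30% | 5% vs 35% |
|---|---|---|---|---|
| 0.90 | 1.000 | 1.005 | 1.011 | 1.016 |
| 0.80 | 1.000 | 1.016 | 1.033 | 1.050 |
| 0.70 | 1.000 | 1.028 | 1.057 | 1.087 |
| 0.60 | 1.000 | 1.041 | 1.083 | 1.127 |

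Columns are h1 versus h0. If the factor is commoner at home, the shares swap and the result is the reciprocal, for example 1/1.083 = 0.92 and 1/1.127 = 0.89. Equal detection gives 1.00 throughout.

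Only the corner value of 1.127 passes the plan's 10% threshold. These figures cover ascertainment alone. Confounding by a true difference in risk between settings or services would be additional, and the documents give nothing from which to size it.

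**The case against.** The strongest reply is that ascertainment is the same by design. Every participant's history is reviewed whatever was said at the interview, so an ulcer not mentioned on the telephone is still found if it was documented. No foot examination is specified at 12 months for either group, so face-to-face contact is not shown to add detection. This stands: the telephone call alone does not establish bias. It does not remove the possibility that the records themselves differ in completeness or timing.

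A second reply is that age, diabetes, neuropathy, arterial disease, cardiac disease and dialysis duration are already bold in Table 9 and may absorb much of any difference between settings. That is fair for measured case mix. It does not cover documentation or service-level practice.

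Third, a predefined statistical analysis plan is promised and not shown. It may handle centre. But the article does more than stay silent: it names a list, and an analysis plan that follows the list would leave these variables out.

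Stronger readings are tempting and are not supported:

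- **Uncontrolled bias in every model.** A reader might infer this, but the article fixes a candidate list, not the final models, and shows no difference in detection.
- **Full transfer of the home:satellite ratio to other risk factors.** The ratios of 0.63 to 0.95 concern setting itself, which is not a listed exposure. The carry-over is much smaller, as the table shows.
- **Standard errors that ignore clustering by unit.** The documents state neither the number nor the size of units and do not say that clustering will be ignored. The usual design effect concerns exposures constant within a unit, and Table 9 lists none.

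**Conclusion.** The point holds as a gap in a stated covariate list. Table 9 omits setting, modality and health service although all are collected or known, and although recruitment route and follow-up contact differ by setting. Differential ascertainment is possible rather than shown. With assumed detection of 0.95 in satellite units and 0.60 to 0.90 at home, the carry-over to another risk factor's ratio is modest: about 1.01 to 1.08 with home shares of 10% versus 30%, 1.13 at the extreme of 5% versus 35%, and none if the factor is unrelated to setting. The size rests wholly on those assumed rates and shares. The omission does not undermine the study, but it is worth correcting because the correction is nearly free.

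**What to change.** Add dialysis setting (satellite or home), or modality where it is not collinear with setting, and health service to Table 9. Use them in the ulcer models as adjustment covariates or as Cox strata. Keep them in rather than leave them to the 10% rule, since most of the carry-over values above fall below that threshold. Report the risk-factor estimates with and without them, so that readers can see whether they matter.

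No new data are needed. As covariates, setting takes one parameter and three services take two, so three in all; replacing setting with the three-level modality variable would make it four. As strata they add no coefficients: 2 × 3 = 6 strata, with some loss of information if any stratum has few events.

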### Primary outcome

The primary outcome in this prospective observational cohort study will be:new foot ulcer(s) (including new and reoccurring ulcers).

A foot ulcer will be defined as a ‘full thickness skin break that is distal to the ankle joint, and may extend into or through the dermis and involve deeper structures such as bones, tendons, joint capsules and ligaments’ [27, 73]. Current foot ulcers (i.e. ulcers present at baseline appointment) that healed and re-ulcerated during the follow-up period will also be recorded as new foot ulcers. At the 12-month follow-up appointment, participants will self-report whether they developed a new foot ulcer since their baseline appointment. This information will be verified by reviewing participants’ medical records. All new foot ulcers documented at the follow-up appointment will be differentiated into ‘new’ and ‘reoccurring’ ulcers. All medical histories of participants will be reviewed to determine whether any new foot ulcers occurred during the 12-month follow-up period.

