### Data handling and statistical analysis

Data will be entered into a Microsoft Excel® spread sheet for the development of an analytical file. A predefined statistical analysis plan will be established between an experienced biostatistician ([name]) and the research team prior to commencing the analysis. Baseline sociodemographic, health-related quality of life and clinical characteristics of participants will be calculated and expressed as mean ± standard deviation or median (25^th^ to 75^th^ percentile) for continuous variables and number (proportion) for categorical variables. For comparison of baseline variables between different groups (for example, foot ulcer or no foot ulcer), independent samples *t*-tests will be calculated for continuous variables and chi-square (*χ*^2^) tests for categorical variables. Unadjusted foot ulcer incidence rates will be calculated for number of events per 1000 person-years. Multivariate Cox proportional hazards models will be used to assess predictors of new foot ulceration and time to event secondary outcomes. Logistic regression will be used for binary outcomes, such as prevalence of foot ulcerations.

Base regression models will be developed to fit each risk factor one at a time with other variables including baseline demographics and possible confounders as described in Table 9 [9, 76, 77], and statistical significance will be assessed. As a sensitivity analysis, we will also use forward selection when building models with *P*-values set at 0.1. Confounders will be retained if they change the estimated associations between risk factors and the outcome by 10 % or more, or are significant at the 5 % level in adjusted models [78]. After a number of iterations, all risk factors will then be combined in a multivariable regression model. Possible interactions will also be assessed. Strata specific analysis of regression models using diabetes (yes/no) and sex (male/female) will be conducted to assess variables for possible effect modification. Interaction terms will then be included in the regression models if there is evidence of an effect modification from any of these variables. Risk estimates will be presented as hazard ratios and/or odds ratios (depending on the regression model) with corresponding 95 % confidence intervals (CIs). Statistical significance will be set at the conventional level of *P* < 0.05.

**Table 9 Tab9:** Risk factors and potential confounding variables

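### Participants with an open foot ulcer at baseline are followed for a new ulcer from day 0 with current ulcer only a candidate covariate, so some hazard ratios can be biased, modestly if it is adjusted for

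*Protocol article*

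**What the plan says.** All references are to the protocol article; the statistical analysis plan is not shown.

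- **Eligibility** (Participant recruitment, screening and eligibility criteria). Participants must be adults, stable on dialysis and able to consent. The exclusions are refusal of consent and people who "have insufficient English skills to provide informed consent or follow instructions during the project". An open foot ulcer is no bar to entry.
- **Event** (Primary outcome). Any new foot ulcer counts, first or recurrent. Ulcers present at baseline "that healed and re-ulcerated during the follow-up period will also be recorded as new foot ulcers".
- **Time origin** (Secondary outcomes). Time to onset is the "number of days between the baseline appointment and the development of a new foot ulcer", with no separate origin for people who start with an ulcer.
- **Model** (Data handling and statistical analysis). "Multivariate Cox proportional hazards models will be used to assess predictors of new foot ulceration". Strata are named for diabetes and sex, and forward selection is named as a sensitivity analysis.
- **Covariate** (Table 9). "Current foot ulcer present at baseline" appears in bold, and the footnote says: "Potential confounding variables that will be considered in the regression models are boldface". Confounders stay if they change an estimated association by 10% or more, or are significant at 5%.
- **Data held** (Table 7). Location, type and duration of a current ulcer are recorded.

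**The concern.** Two different processes share one risk set. An ulcer-free participant can have an event anywhere on either foot from day 0. A participant with an open ulcer cannot have one at that site until it heals, yet the unhealed days count as time at risk. A factor that slows healing, arterial disease for instance, lengthens the period in which the index-site event cannot happen, and so can look less harmful than it is. The HR for current ulcer, itself a listed risk factor, is pulled down for the same reason.

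There is also a question of temporal order. CRP and albumin are averages of the three latest results, podiatry attendance covers the previous 12 months, and footwear is assessed at baseline. In someone with an open ulcer these may partly be consequences of it. The article's Conclusion promises a temporal sequence from risk factor to ulcer, which is weakest in this subgroup.

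**Working it through.** **1. Who can have an event, from the text alone**

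| Course | Counted as |
|---|---|
| No ulcer at baseline, ulcer later | Event |
| Open ulcer, heals, breaks down again | Event; its time includes the unhealed days |
| Open ulcer never heals, new ulcer elsewhere | Event |
| Open ulcer never heals, none elsewhere | No event |

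**2. HR for current ulcer itself.** The article gives no healing rates, so a range is assumed. With healing rate *h* per year, the expected share of the year spent after healing is s = 1 - (1 - e^(-h))/h. If the hazard while the ulcer is open is a fraction *r* of the usual hazard (ulcers at other sites only), the HR shrinks by roughly s + r(1 - s).

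| h | s (r = 0) | factor at r = 0.5 |
|---|---|---|
| 2 | 1 - 0.865/2 = 0.57 | 0.78 |
| 1 | 1 - 0.632/1 = 0.37 | 0.68 |
| 0.5 | 1 - 0.393/0.5 = 0.21 | 0.61 |

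Putting current ulcer into the model does not repair this particular HR.

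**3. HR for another risk factor.** Simulated cohorts, all inputs assumed: true HR 2.0, factor present in 50%, odds ratio 4 between factor and open ulcer, base hazard 0.10 per year, healing rate halved by the factor, 12 months' follow-up. Selected results:

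| Ulcer prevalence | Healing rate without / with factor | r | Not adjusted | Adjusted for current ulcer | Ulcer-free only |
|---|---|---|---|---|---|
| 5% | 2 / 1 | 0 | 1.90 | 1.98 | 2.00 |
| 15% | 2 / 1 | 0 | 1.75 | 1.97 | 2.00 |
| 15% | 2 / 1 | 0.5 | 1.90 | 1.99 | 2.03 |
| 15% | 1 / 0.5 | 0 | 1.68 | 1.97 | 2.00 |
| 15% | 1 / 0.5 | 0.5 | 1.86 | 1.99 | 2.01 |

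- Largest downward shift without adjustment: 1.68/2.00 = 0.84, or -16%.
- If an open ulcer also triples later hazard, the unadjusted HR is 0.96 to 1.23 times the ulcer-free HR, so the shift can reach +23%. The upward part is ordinary confounding by the omitted covariate.
- With adjustment, the ratio to the ulcer-free HR is 0.95 to 1.01 across all runs, simulation noise included.
- About 1 to 8% of the cohort (430 x 0.01 to 0.08, or 4 to 34 people) have a never-healed ulcer and no event.

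Harsher assumptions: ulcer-free hazard 0.12 per year, healing 1.5 per year (halved by the factor), re-ulceration 0.6 per year (doubled by the factor), death 0.13 per year, no risk at other sites. The adjusted HR is then 1.93, 1.87 or 1.82 at 5, 10 or 15% prevalence. The largest shift is (2.00 - 1.82)/2.00 = 9%.

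**4. Would the retention rule keep current ulcer?** On the HR scale, adding it changes the factor's estimate by (1.98 - 1.90)/1.90 = 4% in the first row of the step 3 table, below the 10% trigger, and by (1.97 - 1.75)/1.75 = 13% in the second, above it. At 5% prevalence only 430 x 0.05, about 22 participants, have an ulcer. Step 2 shows that their HR is pulled down, which makes 5% significance harder to reach. Whether the adjustment is made is left to the data.

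**The case against.** **Other sites count.** A reader might infer that anyone whose ulcer never heals is automatically a non-event. The article does not support that: any new foot ulcer counts for the participant. A reader might also infer that a real risk factor vanishes inside the current-ulcer group. With the harsher rates and death ignored, the 12-month re-ulceration risk is 1 - (a e^(-b) - b e^(-a))/(a - b) for healing rate a and re-ulceration rate b. That gives 23.4% without the factor (a = 1.5, b = 0.6) and 24.2% with it (a = 0.75, b = 1.2). But this near-null result depends on allowing no risk elsewhere. With other-site hazard at 1, 3 or 5 times the ulcer-free rate, the subgroup HR is about 1.3, 1.5 or 1.8. This objection stands.

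**The bias is small beside sampling error.** On the log scale the adjusted bias is ln(2.00/1.93) = 0.04 to ln(2.00/1.82) = 0.09. With about 70 to 95 events under those rates, the standard error of the log HR is near 0.25. This also stands for the other risk factors.

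**It is partly handled.** Current ulcer is in Table 9, all risk factors are later combined in one model, and the larger unadjusted shifts would tend to trip the 10% rule. So -16% to +23% marks the outer edge, not the expected result. The one-at-a-time models are still left to that rule.

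**Temporal order is ordinary confounding.** An open ulcer that raises CRP and also raises later risk is a prior common cause, and adjustment addresses it. That is largely right, provided the adjustment is made. Table 9 enters only presence, not duration or type, so some may remain. No figure was derived for this part.

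**A persisting ulcer is not a new one.** Correct; the outcome definition need not change.

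**These are details for the analysis plan.** A restricted analysis and stratification often belong there, so their absence is not itself the fault. The event definition, time origin and conditional covariate status are fixed in the article.

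**Conclusion.** The point holds in a limited form. The text establishes that participants with an open ulcer are enrolled, are followed from the baseline appointment, and at the index site can have an event only after healing. Adjustment for current ulcer is conditional.

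It does not establish that the study's HRs are distorted. That stronger reading needs a baseline ulcer prevalence and healing rates, and the article gives neither. Under the assumed inputs the bias in other risk factors is roughly 0 to 9% of a true HR of 2.0 once current ulcer is in the model. It is larger and of uncertain direction (about -16% to +23%) if it is not. The HR for current ulcer stays biased low either way. The sample size of 430 is not affected.

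This is a worthwhile, inexpensive tightening of the primary analysis, not a defect that undermines the study.

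**What to change.** 1. In every Cox model for new foot ulceration, stratify the baseline hazard by current ulcer at baseline, or force it in as a covariate, and take it out of the retention rule. Stratifying yields no HR for current ulcer. If that HR is wanted, as Table 9 implies, report it from the covariate version and say that it is likely to understate the risk.
2. Pre-specify a Cox analysis restricted to participants with no open ulcer at baseline, reported beside the whole-cohort analysis and used when interpreting CRP, albumin, footwear and podiatry attendance.

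Both use data already recorded, so the cost is wording. Under the harsher assumed rates, participants with a baseline ulcer supply 8 to 21% of events. Losing them widens the restricted analysis's intervals on the log scale by 1/√0.92 = 1.04 to 1/√0.79 = 1.13, or 4 to 13%.

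Starting index-site risk at the date of healing is not recommended unless healing dates are collected, which the article does not say. No new rule is needed for ulcers at other sites, because the outcome definition already counts them.
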